### Recruitment

Subject recruitment will be mainly carried out in outpatient clinics. Recruitment advertisement reviewed by the ethics committee will be performed in physical examination centers, outpatient halls, and other places where potential subjects gather to promote the recruitment. The investigators will be experienced physicians who are familiar with the trial process. A printed standardized protocol and an informed consent form will be presented during the investigation. To promote participant retention and complete follow-up, we will inform the subjects that their condition may improve after participating in this clinical study, and they can also obtain more medical advice and guidance related to this disease during the trial. Participants may also contribute to the research on the prevention and treatment of hyperlipidemia in TCM, which has social significance. The enrollment will be performed after the investigators fully introduce the detailed trial process, probable benefits, and potential risks to the eligible participant. The investigators will fulfill the case report form (CRF) after the participants have signed the informed consent form. All data collected from participants including personal information will be kept confidential in this trial.

### Interventions

Included participants in the treatment group will receive QSHY granules, while QSHY-simulated granules as placebo will be applied in the control group. Both groups of participants will receive regular health education, including diet control, exercise, and behavior modification. (1) Diet adjustment: diets with low sugar, low fat, and high vitamin will be recommended; (2) strengthen physical exercise: moderate metabolic equivalent exercise will be recommended for more than 30 min each time, 4 times a week; and (3) adjust emotion and keep a good mood.

The QSHY are compound preparations of 5 Chinese herbs, Artemisiae scopariae herba (Yin Chen), Polygoni cuspinati rhizome et radix (Hu Zhang), *Curcumae longae* rhizome (Jiang Huang), Gardeniae fructus (Zhi Zi), and Herba hyperici japonici (Tian Jihuang), packaged in consecutively numbered drug containers. The number was distributed according to the randomized number. The placebo will have an identically packaged appearance, weight, and taste compared to the QSHY granule. Both QSHY granule and placebos will be produced by Jiangyin Tianjiang Pharm Co. Ltd., Jiangsu, China. Participants will be advised to take one pack after meal, twice a day. The drugs are stored in the clinical trial base certified by Good Clinical Practice (GCP) and are managed and distributed in an independent clinical medicine center. The number of drugs received, taken, and returned by the patients will be recorded in detail by the research doctors at each visit. During the experimental period, non-pharmacologic care is permitted, but other TCM herbs and Western medication for lipid-lowering or fatty liver treatment will be prohibited.

Participants will be provided the information of the treatment and be advised not to take concomitant medications or change the dose and frequency of drugs autonomously. To facilitate completion, participants will be suggested to contact the arranged physicians for any questions raised about this trial. The drugs left over will be returned, and the related medication compliance will be calculated. Any combination of medications will be recorded in detail. Participants will be recommended to visit the outpatient clinic regularly for post-trial care.

### Study visit overview

The visits in this trial are designed as 5-time points during 24 weeks of intervention: baseline, 6 weeks ± 5 days after enrollment, 12 weeks ± 5 days after enrollment, 18 weeks ± 5 days after enrollment, and 24 weeks ± 5 days after enrollment. At each visit time point, participants will be tested the laboratory index or recorded vital signs according to the study schedule. The detailed flow path information is shown in Fig. 2.

**Fig. 2 Fig2:**
[figure not shown]
Study schedule of enrollment, interventions, and assessments. QSHY, Qu-Shi Hua-Yu granule; LDL-C, low-density lipoprotein cholesterol; TC, total cholesterol; TG, triglyceride; HDL-C, high-density liptein cholesterol; Apo, apolipoprotein; FBG, fasting blood glucose; SF-36, Medical Outcomes Study Item Short-Form Health Survey; TCM, traditional Chinese medicine; BMI, body mass index; WHR, waist-to-hip ratio; HCG, human chorionic gonadotropin

Blood samples will be collected from participants when they undergo blood examination and temporarily kept in evacuated and promoting coagulating tubes at 4 °C. After blood samples are centrifuged (4 °C, 3500 rpm/min, 10 min), serum samples will then be collected in Eppendorf tubes and stored orderly in refrigerators for clinical trials at − 80 °C.

### Adverse events process

If adverse events (AEs) occur, the researchers will judge its relationship with the trial, and take necessary measures to ensure the safety and rights of the participants. The severe adverse events (SAEs) should be reported to the IRB of Shuguang Hospital within 24 h. If moderate or severe adverse reactions judged to be related to the clinical trial occur in more than 25% of the total participants, this clinical trial will be terminated early.

### Outcomes

The primary outcome in this study is the change in LDL-C from baseline to week 12. The secondary outcomes are the changes in fasting serum TC, TG, HDL-C, non-HDL-C, apolipoprotein (Apo) A-I, ApoA-II, ApoB, and fasting blood glucose at 12-week assessment and 24-week assessment, and the change in the ratio of TC/HDL-C at 12-week assessment and 24-week assessment. All mentioned serum biochemical markers will be measured at baseline, 12-week, and 24-week after randomization. The measurement of life quality will be assessed by the Medical Outcomes Study Item short-Form Health Survey (SF-36) questionnaire. The changes in the syndrome of TCM for participants will be measured using four TCM diagnostic methods and the Scores of TCM syndrome Scale. Other outcomes are blood pressure, heart rate, body mass index (BMI), and waist-to-hip ratio (WHR).

Safety indexes are blood and urine routine examination and results of serum liver function test including AST, ALT, alkaline phosphatase (ALP), and serum renal function test including creatinine (CR) uric acid (UA) and blood urea nitrogen (BUN). Adverse events that occurred in the trial period will be monitored at each visit. All collected adverse events and their degree will be recorded with followed medical intervention in the CRF.

### Sample size

According to the previous results from a single-center clinical observation, after being treated with QSHY decoction, the fasting serum TC level decreased by 23.84% compared with baseline, and the fasting serum TC level in the control group decreased by 12.71% compared with baseline. It is expected that the decrease of fasting LDL-C level in the QSHY granule group will increase by 15% compared with placebo. Assuming *a* = 0.05, *β* = 0.2, *n*_*T*_: *n*_*C*_ = 1:1, *ẟ* = 0, *π*_*C*_ = 0.155, and *π*_*T*_ = 0.305, according to the formula of the optimal sample size, 94 samples in each group will be obtained. Considering the leakage rate of 10%, there will be at least 105 cases in each group.
$$ {n}_T={n}_C=\frac{{\left({z}_{1-\alpha }+{z}_{1-\beta}\right)}^2\left[{\pi}_T\left(1-{\pi}_T\right)+{\pi}_C\left(1-{\pi}_C\right)\right]}{{\left[\left({\pi}_T-{\pi}_C\right)-\delta \right]}^2} $$

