### Statistical analysis

The statistical analysis will be performed by an independent statistician. After the trial protocol is determined, the statistician is responsible for formulating the detailed statistical analysis plan in consultation with the principal investigator. Statistical analysis will be conducted using the SAS version 9.1 statistical software.

The primary analyses for this study will adopt the intention-to-treat (ITT) principle. The full analysis set [41] includes participants who met the inclusion and exclusion criteria and received at least one evaluation after randomization. The per-protocol set (PPS) includes participants who had good compliance (80–120% of the trial drugs were used), did not take prohibited drugs during the trial, and completed the CRF. Safety analysis will be conducted based on a safety analysis set including participants who have received at least one intervention and safety evaluation.

Participants can withdraw at any time and will be recorded the reason for withdrawal. Participants who discontinue or deviate from intervention protocols will be informed by interviewers to get the reason for dropout. The original data of all withdrawn and terminated cases should be kept and recorded for further analysis. The last observation of participants who dropped out or existing missing data will be carried forward as the final data.

Continuous variables will be presented as mean ± standard deviation [42] or median with quartile range, according to the distribution. An independent *t*-test or the Mann-Whitney *U* test will be conducted to compare the differences between the groups. Dichotomous variables will be presented as frequency and percentage and analyzed with the chi-square test or Fisher’s exact test. Subgroup analyses will be performed based on groups with high heterogeneity if necessary.

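### The sample size comes from a one-sided two-proportion formula, but the primary outcome is a continuous LDL-C change, so the stated 80% power is not that of the planned primary test

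*Protocol article*

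**What the plan says.** The Outcomes section defines the endpoint: "The primary outcome in this study is the change in LDL-C from baseline to week 12". The Statistical analysis section gives the test for continuous variables: "An independent *t*-test or the Mann-Whitney *U* test will be conducted to compare the differences between the groups". Variables of the other type are handled separately: "Dichotomous variables will be presented as frequency and percentage and analyzed with the chi-square test or Fisher’s exact test". The Outcomes section gives no threshold or responder definition for LDL-C.

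The Sample size section starts from an earlier single-centre observation of total cholesterol (TC) under the QSHY decoction. In the treated group "the fasting serum TC level decreased by 23.84% compared with baseline"; the corresponding fall among controls was 12.71%. It then moves to LDL-C: "It is expected that the decrease of fasting LDL-C level in the QSHY granule group will increase by 15% compared with placebo". The design values follow: "Assuming *a* = 0.05, *β* = 0.2", 1:1 allocation, a margin of 0, and π values of 0.155 (control) and 0.305 (treatment). The printed formula uses z at 1 − α and the binomial variances π(1 − π). The result is 94 per group, raised to 105 for 10% loss. The article does not say what the π values represent.

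**The concern.** A sample size calculation supports a power claim only if its effect measure and variance are those of the planned test. Here the test compares LDL-C changes, so power depends on the difference in mean change and its SD. The calculation instead uses a difference between two proportions, with a variance fixed entirely by the π values. No SD of LDL-C change appears in the article.

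The gap between the π values is exactly 0.15, which matches the 15% greater fall expected in LDL-C. The natural explanation is that percentage falls in a lipid level were entered as if they were proportions of patients. That is an inference, because the article does not define them.

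Two lesser weaknesses sit alongside. The 15-point LDL-C effect is not derived from the cited data, which concern TC and show a gap of 23.84 − 12.71 = 11.13 points. The formula is also one-sided at 5%, although the text never states the sidedness.

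At stake is the figure that justifies the size of a placebo-controlled trial. As it stands, a result cannot be judged against a stated power for the primary comparison.

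**Working it through.** **Reproducing the plan's figure.** Inputs from the Sample size section: π_T = 0.305, π_C = 0.155, δ = 0, α = 0.05, β = 0.2.

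- Variance term: 0.305 × 0.695 + 0.155 × 0.845 = 0.2120 + 0.1310 = 0.3430.
- One-sided, as printed: (1.645 + 0.842)² × 0.3430 / 0.15² = 94.2, which matches the printed 94 (strict rounding up would give 95).
- Loss: 94 / 0.9 = 104.4, rounded up to 105, as printed.
- Two-sided, same formula: (1.960 + 0.842)² × 0.3430 / 0.15² = 119.6, or 120 per arm. This does not match, so the printed figure is one-sided.

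The stated 80% (79.9% at exactly 94) is therefore the power of a one-sided comparison of 30.5% with 15.5%.

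**What the formula implies for a comparison of means.** Read on a percentage-change scale, the binomial variances amount to an average SD of √(0.3430 / 2) = 0.414, or about 41 percentage points. This number comes from the π values and not from LDL-C data.

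**What 94 per arm gives in a two-sample t-test.** The standard error of the difference is SD × √(2/94) = 0.1459 × SD. Solving for 80% power with the t distribution:

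- two-sided 5%: standardised difference 0.41 (normal approximation 2.802 × 0.1459 = 0.409);
- one-sided 5%: standardised difference 0.36 (normal approximation 2.486 × 0.1459 = 0.363).

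These two values need no SD. To turn them into power for a given LDL-C difference, an SD must be assumed. I take 20 to 30 percentage points for the SD of percentage change; the article gives no value.

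| Difference | SD | Power, two-sided 5% | Power, one-sided 5% |
|---|---|---|---|
| 15 points | 20 | 99.9% | over 99.9% |
| 15 points | 25 | 98% | 99% |
| 15 points | 30 | 93% | 96% |
| 11.13 points | 20 | 97% | 98% |
| 11.13 points | 25 | 86% | 92% |
| 11.13 points | 30 | 72% | 81% |

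At two-sided 5%, power is exactly 80% only if the SD is about 36.5 points (15 / 0.411) for a 15-point difference, or about 27 points (11.13 / 0.411) for an 11.13-point difference. Nothing in the article says where the true SD lies.

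**The case against.** The strongest reply is that the number of patients may well be adequate. That stands. At the planned 15-point difference, every assumed SD gives more than 90% power. At the formula's own one-sided 5%, all six scenarios exceed 80%. The only value below 80% (72%) needs the smaller effect, the largest assumed SD and a two-sided test together.

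A reader might therefore infer from the wrong formula that the trial is underpowered. The article does not support that: it gives no SD, and the scenarios fall mostly on the favourable side. Nor should a reader put the cited TC falls into the printed formula and treat the larger sample size as evidence of a shortfall. That would reuse the variance that does not apply to this endpoint.

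A second reply is that the π values may be responder rates explained in a fuller document. The article does not exclude this, but it would not rescue the claim. Responder rates would describe an endpoint that the Outcomes section does not list, and the power would still not be that of the t-test or Mann-Whitney comparison.

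A third reply is that the expected LDL-C effect need not equal the TC gap, since they are different lipids. This is fair. The gap between 11.13 and 15 shows only that the assumption lacks a derivation, and 11.13 serves here as a sensitivity value and not as the right LDL-C effect.

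Finally, this is not a detail left to an unseen analysis plan. The formula, its inputs and its result are printed, and they conflict with the endpoint and test printed in the same article.

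**Conclusion.** The point holds in this form: the calculation is arithmetically correct but answers a different question. The stated β of 0.2 is not a property of the planned primary test, whichever meaning the π values have. The power of that test is undetermined because no SD of LDL-C change is given.

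Under the assumed SD of 20 to 30 points, power with 94 per arm is 99.9% to 93% for 15 points (two-sided 5%). For 11.13 points it is 97% to 72% two-sided and 98% to 81% one-sided. These ranges rest on the assumed SD, on reading the change as a percentage, and on a t-test. They establish neither underpowering nor a need for more patients. What is wrong as written is the power statement, and it should be corrected because the trial's size rests on it.

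**What to change.** Keep N = 210. Delete the proportions formula and the π values, and replace them with a two-sample comparison of means on the week-12 LDL-C change. State:

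- whether the test is one-sided or two-sided, and at what α;
- whether the change is absolute or percentage, and, if percentage, that the assumed effect is in percentage points;
- the SD of the change and its source, either published or a blinded pooled estimate from patients already enrolled (the Trial status section reports 102);
- the basis for the assumed 15-point LDL-C effect, given that the cited data are for TC.

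Restate the power without reference to proportions: 94 evaluable per arm gives 80% power for a standardised difference of 0.41 at two-sided 5%, or 0.36 at one-sided 5%. Add power at a smaller effect as a sensitivity check; 11.13 points is a convenient choice.

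The cost is a wording amendment, which needs re-approval by the ethics committee under the Ethics issue section, and one blinded SD estimate if no published value is used. No extra patients and no unblinding are needed. The stated power may turn out less favourable than 80%.

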### Randomization and allocation

The consecutive random sequence of 2 groups is provided by the clinical medicine center with SAS version 9.1 statistical software. Eligible participants will be randomly allocated into the QSHY group or the placebo group in a 1:1 ratio. The random sequence will be sealed in opaque envelopes and locked in the independent clinical medicine center. The allocation concealment will be maintained until all the data of each participant in each visit had been uploaded and locked.

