## Discussion

Hyperlipidemia is a companion to many metabolic diseases, such as NAFLD and coronary heart disease. According to previous studies, QSHY can improve liver function and blood lipids, including TC, LDL-C, and TG of HFD rodent models [34], and no adverse reactions were found [35, 37]. Three previous clinical trials in China [33, 34, 43] have shown that QSHY significantly reduces ALT and AST in patients with NAFLD and can reduce serum TG and TC, which indicates that QSHY has a therapeutic effect on patients with NAFLD and hyperlipidemia. However, the data presented are all based on the inclusion criteria of NAFLD patients, and precise data of QSHY for hyperlipidemia is still lacking. We designed this protocol to explore whether QSHY is an effective treatment of hyperlipidemia.

We designed a randomized, double-blind, placebo-controlled clinical trial based on a superiority framework. Hyperlipidemia can be improved by diet control and regular exercise. in this study, we include participants with mild to moderate abnormalities in LDL value and strengthened health education for the subjects. We excluded patients who must undergo lipid-lowering therapy, such as those who are at high or very high risk of ASCVD, or had unstable or severe arterial disease events 6 months before screening, to avoid violating ethical requirements. Therefore, we chose placebo as a comparator. The use of placebo control can clarify the absolute efficacy of the study drug and have higher efficiency.

A high level of LDL-C, not only a biomarker, appears to be a causal factor of the pathophysiology of ASCVD. According to the guidelines for the management of dyslipidemias issued by the European Society of Cardiology/European Atherosclerosis Society (ESC/EAS) in 2019 [44], serum LDL-C level is recommended as the main outcome for screening, diagnosis, and management of lipid modification to reduce cardiovascular risk. Thus, we set LDL-C, not TC or TG, as the primary outcome in this trial. According to the 2002 guiding principles of clinical research on new drugs of traditional Chinese medicine, participants are recruited according to the conventional TCM syndrome identification before randomization.

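### The sample size rests on a one-sided 5% critical value that the protocol never declares; with a two-sided 5% test the printed formula gives about 70% power, not 80%

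*Protocol article*

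**What the plan says.** The Sample size section opens its calculation with "Assuming *a* = 0.05, *β* = 0.2", equal allocation, a margin of zero, and proportions of 0.155 (control) and 0.305 (treatment). The formula has z(1-alpha) plus z(1-beta), squared, in the numerator, with the sum of the two binomial variances. The result is stated as "according to the formula of the optimal sample size, 94 samples in each group will be obtained". Loss is then added: "Considering the leakage rate of 10%, there will be at least 105 cases in each group".

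Three other places bear on the direction of the test:

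- **Statistical analysis:** "An independent *t*-test or the Mann-Whitney *U* test will be conducted to compare the differences between the groups". Dichotomous variables get a chi-square or Fisher's exact test. The section gives neither a direction nor a significance level.
- **Discussion:** the trial is called a "placebo-controlled clinical trial based on a superiority framework". Again no direction or level is given.
- **Blinding:** the first unblinding releases group membership without saying which group is which. The arms are identified at a second unblinding, after the analysis.

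The primary outcome (Outcomes section) is the change in LDL-C from baseline to week 12, a continuous variable.

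**The concern.** In this formula z(1-alpha) at alpha = 0.05 is 1.645, the critical value of a one-sided 5% test. A two-sided 5% test would use z(1-alpha/2) = 1.960. The only sign of a one-sided design is that subscript. The rest of the article reads as though an ordinary undirected comparison is planned.

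The choice matters in either case:

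- If the analysis is two-sided at 5%, the stated beta of 0.2 does not go with 94 per group.
- If it is one-sided at 5%, the chance of falsely declaring QSHY superior is 5%, twice the 2.5% in that direction under a two-sided 5% test. The article gives no reason for accepting this.

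Left open, the success criterion is ambiguous as well. A result in favour of QSHY with a two-sided p-value between 0.05 and 0.10 could be reported as a success or as a failure.

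**Working it through.** **Inputs (Sample size section).** alpha = 0.05, beta = 0.2, control proportion 0.155, treatment proportion 0.305, margin 0, ratio 1:1, loss 10%.

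**Common terms.**
- Variance sum: 0.305 × 0.695 + 0.155 × 0.845 = 0.211975 + 0.130975 = 0.34295
- Squared difference: (0.305 − 0.155)² = 0.0225

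**Step 1: reproduce the stated figure.** The printed formula with the one-sided value gives

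n = (1.6449 + 0.8416)² × 0.34295 / 0.0225 = 94.24

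This is the stated 94, rounded down. Power at 94 is Φ(0.15/√(0.34295/94) − 1.6449) = 79.9%, so the rounding is immaterial. The allowance for loss also reproduces: 94/0.9 = 104.4, so 105.

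**Step 2: could a two-sided calculation have produced 94?** Per-group sizes for 80% power:

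| Variant | One-sided 5% | Two-sided 5% |
|---|---|---|
| Unpooled (the printed formula) | 94.24 | 119.6 |
| Pooled | 97 | 123 |
| Pooled, continuity-corrected | 110 | 136 |

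No two-sided variant comes near 94.

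**Step 3: same inputs, two-sided 5%.**
- Size needed: (1.9600 + 0.8416)² × 0.34295 / 0.0225 = 119.6, so 120 per group. After 10% loss, 120/0.9 = 133.3, so 134 per group and 268 in total, against 105 and 210 planned.
- Power at 94 evaluable: Φ(0.15/√(0.34295/94) − 1.96) = Φ(2.483 − 1.960) = 70.0% (68.8% with pooled variance).
- Power at 105, with nobody lost: Φ(0.15/√(0.34295/105) − 1.96) = Φ(2.625 − 1.960) = 74.7% (73.7% pooled).

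**Step 4: what carries over to a corrected calculation.** The ratio of the two size requirements is (2.8016/2.4865)² = 1.27 and does not depend on the proportions. Any normal-approximation recalculation, including one for a mean change, that kept z(1-alpha) at 5% would ask for about 21% fewer patients than a two-sided 5% test needs (1 − 1/1.27). This says nothing about the actual power for LDL-C, which needs a mean difference and a standard deviation.

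**Step 5: which direction does the described analysis fit?** A one-sided superiority test needs to know which arm is QSHY. The Blinding section has the analysis completed while the arms are still unidentified. A two-sided test can be run that way. A one-sided test would have to be computed in both directions, with the relevant one picked once the labels are known. The t-test and Mann-Whitney test are ordinarily run two-sided unless a direction is declared, and the ordinary chi-square test has no direction.

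**The case against.** **Nothing is miscalculated.** A reader might infer that 94 is an arithmetic mistake. It is not: z(1-alpha) is printed openly, and 94 and 105 both follow from it. This stands in full. The defect is an undeclared and unjustified choice of level that is not carried into the analysis section.

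**The article never says two-sided.** A reader might infer an express contradiction between the Sample size and Statistical analysis sections. There is none. A superiority framework is compatible with a directional test, and t-tests and Mann-Whitney tests can be run one-sided. The chi-square and Fisher tests are for dichotomous variables, not the primary outcome. That the described analysis is two-sided is an inference from usual practice and from the order of unblinding. It is a reasonable inference but not a quotation.

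**A statistical analysis plan may declare the direction.** It may, and the analysis section's silence on its own would be no fault. But that plan cannot leave the Sample size section as it stands. If it says two-sided 5%, the stated beta is wrong for the stated number. If it says one-sided 5%, the sample-size text relies on a level that it neither names nor defends.

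**70% is not the power of this trial.** A reader might infer that the LDL-C comparison has only 70% power. The document does not support that. The printed formula compares two proportions, whereas the primary analysis compares a continuous change, and its standard deviation is not given. Neither 80% nor 70% is the power of the primary analysis.

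**Conclusion.** The point holds in a limited form. The planned number depends on a one-sided 5% critical value that the protocol article neither declares nor justifies, while the analysis it describes fits a two-sided comparison better. If the test is two-sided at 5%, the stated 80% falls to about 70% at 94 evaluable per group, or about 75% if all 105 are evaluable. Reaching 80% would take 120 per group before loss.

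These sizes rest on two conditions: that the test is two-sided at 5%, which the article does not state, and that the printed two-proportion formula and its inputs are taken at face value. They show that the stated error rates and the described analysis do not fit together. They do not measure the power for LDL-C. It should be settled because it fixes the error rate of the primary test, and a choice of direction made after unblinding would not be credible.

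**What to change.** Before unblinding, amend the protocol, and bring the analysis plan into line with it:

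1. State that the primary test is two-sided at 5%, equivalently one-sided at 2.5%.
2. Replace z(1-alpha) by z(1-alpha/2) in the sample-size calculation.
3. Keep the total at 210 and restate the power that it gives. Preferably take this from a calculation for the between-group difference in mean LDL-C change, with the assumed difference and standard deviation stated. If the 70% figure is quoted at all, label it as conditional on the proportions formula.

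The cost is one sentence on the test, a revised calculation, ethics committee reapproval of the amendment (required by the Ethics issue section), and a power figure that, on the printed inputs, is less favourable. No extra patients are needed. The timing allows it: the Trial status section reports 102 enrolled, and the Blinding section has the final statistical plan confirmed before the database is locked and first unblinded.
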